#### **6.4.5. Steering Committee**

A Steering Committee will be convened that will be responsible for providing overall guidance to the sponsors on the study protocol, the scientific merit of proposed substudies, the execution of the trial, the review of recommendations from the DSMB and the oversight of study publications. A separate charter will document specific policies and procedures of the Steering Committee.

#### **6.5. Economic Evaluation**

Following completion of the data collection, health care resources will be estimated in 3 categories to conduct the cost analyses. First, the data collected on health care outcomes (hospitalizations and revascularization procedures) will be summarized. Second, the resources needed to provide lipid lowering treatment (including drugs, physician visits and laboratory monitoring) will be estimated from this trial, the literature, and product labeling. Third, resources needed to provide care for adverse events associated with treatment will be estimated from this trial and the literature.

Market-specific costs for the resources described above will be applied to determine the cost of care (including adverse events) and the costs of care of all cardiovascular outcomes.

Several economic analyses will be performed. These include a description of healthcare resource utilization, net cost analysis (the costs of providing lipid-regulating therapy minus the cost of care for healthcare outcomes) and cost-effectiveness analysis (cost per year of life saved).

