concurrent treatment with either aspirin, beta-blockers or calcium-channel blockers. Results by baseline LDL-C also showed a consistent reduction in risk among the quartiles of this high cholesterol cohort; the lowest such quartile had an average LDL-C of  $\leq 4.39$  mmol/l (170 mg/dl).

Costs of treatment to reduce cardiovascular risk factors may be offset by savings incurred by a reduction in hospital and ambulatory cost associated with myocardial infarction, coronary revascularization and long-term care for patients with existing heart disease. Two types of pharmacoeconomic analyses were undertaken in conjunction with the 4S trial: net cost analysis and cost-effectiveness analysis. These cost analyses incorporated prospectively collected resource utilization data on cardiovascular hospitalizations and revascularization procedures. Decreases in resource utilization during simvastatin therapy (vs. Placebo, all  $p < 0.0001$ ) were shown for the number of hospitalizations for acute cardiovascular disease and CHD events, the number of coronary revascularization procedures and days spent in the hospital for the above events. Net cost analysis showed that 88% of the costs associated with simvastatin treatment could be saved by reductions in hospitalization and procedures over 5.4 years. The cost-effectiveness ratios obtained showed that treatment with simvastatin is cost-effective in the markets studied. The results of the economic portion of this current study will focus on the reduction of healthcare resource utilization associated with lowering LDL-C beyond the targets shown in the 4S study.

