#### **6.2.4 Double-Blind Active Treatment Period**

This period begins at Visit 5 (Week 0). Procedures performed at this visit include an assessment of vital signs, an ECG and physical exam, repeat clinical chemistry/fasting lipid determinations and continued dietary counseling. The ECG and physical exam may be performed between Visits 4 and 5 once a patient's lipid levels qualify them for randomization.

The open-label atorvastatin 10 mg therapy will stop at Visit 5. Qualified patients will be randomized to 1 of 2 blinded treatment groups, either 80 mg atorvastatin or 10 mg atorvastatin. The patient should take the study medication once daily. Neither the investigator nor the study sponsor will be informed of the lipid values of randomized patients (except as noted in section 6.4.1) in order to maintain the blind of the study.

Visits will be at designated intervals during the active treatment period. Patients will be regularly counseled on following the NCEP Step I, Step II (see Appendix A.3) or equivalent diet in order to maintain body weight, and lipid levels. Other procedures such as lipid profiles, clinical laboratory measurements, physical examinations, and electrocardiograms will be performed according to the timetable in Appendix A. Patients will be assessed for the occurrence of adverse events and the change or addition of concomitant therapies at all visits in the double-blind treatment period. Medical resource utilization regarding all hospitalizations and revascularization procedures will be collected.

During the first year of the double-blind period, four follow-up visits are scheduled at weeks 12 and months 6, 9 and 12.

After completion of the first year of active treatment, patients are to have scheduled study visits every six months. At each visit, vital signs, clinical end points, adverse event, and concurrent medication information will be collected. On alternating visits (i.e., annually) in addition to the above, physical examinations and electrocardiograms will be performed and laboratory specimens will be collected.

While on average a patient will be on active treatment for 5 years, the actual length of time for an individual patient will vary based on the study recruitment rate, primary event rate and when the patient was recruited relative to the entire study cohort. Therefore, it is estimated that actual active treatment for a patient could range from approximately 3 to 7 years.

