Assuming a 5 year cumulative **major coronary** event rate in the atorvastatin 80 mg group of 7.02%, a 5 year cumulative **major coronary** event rate in the atorvastatin 10 mg group of 9%, and no dropouts, drop-ins, or noncompliance, a sample size of 6,928 subjects would have 91% power for a one-sided test at alpha of 0.05 and 85% power for a two-sided test at alpha of 0.05. In order to compensate for an estimated 10% dropout/drop-in/noncomplier rate, the study will have a target enrollment of approximately 8,600 subjects  $[6,928/(1-0.1)^2 = 8,553]$  **in order to accumulate the target number of 750 major coronary events in an average follow-up time estimated at 5.5 years** (Lachin, JM, *Controlled Clinical Trials* 2, 93-113 (1981)).

*The sample size estimation shown above was based on assumptions regarding incidence rates for major coronary events (the primary endpoint excluding stroke). It is anticipated that approximately 950 primary endpoints (an additional 200 stroke events) will accrue over the total expected duration of the trial, thereby providing 91% power for a one-sided test at alpha of 0.05 and 85% power for a two-sided test at alpha of 0.05 to detect a 17% reduction in the 5 year cumulative primary endpoint rate for atorvastatin 80 mg relative to atorvastatin 10 mg.*

*<letter, sentence, paragraph deleted>* The power calculations were performed using n-Query Advisor, Version 2.0, by Janet D. Elashoff.

*The steering committee will examine blinded incidence, dropout rate, and other key assumption information when approximately 2 years of completed follow-up data is available and decide whether the proposed target number of events (described in Section 6.1) is appropriate. The sponsor will be approached if a change is proposed.*

#### June 13, 2003 – Amendment 4

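### Section 6.5 defines net cost as therapy cost minus cost of care, so care averted by the 80 mg arm is added to its cost instead of deducted

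*Supplement*

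**What the plan says.** Section 2 names cost-effectiveness among the subsidiary objectives. Section 6.5 describes three groups of resources: hospitalizations and revascularizations, the provision of lipid-lowering treatment, and care for adverse events. Market-specific costs "will be applied to determine the cost of care (including adverse events) and the costs of care of all cardiovascular outcomes".

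It then names the analyses. These include a description of resource use, a "net cost analysis (the costs of providing lipid-regulating therapy minus the cost of care for healthcare outcomes", and a "cost-effectiveness analysis (cost per year of life saved".

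The Introduction presents the same type of analysis differently. It says: "Costs of treatment to reduce cardiovascular risk factors may be offset by savings incurred by a reduction in hospital and ambulatory cost". For the earlier simvastatin trial it reports, as the net cost result, that "88% of the costs associated with simvastatin treatment could be saved by reductions in hospitalization and procedures" over 5.4 years. It adds that the economic part of this study will concentrate on reduced use of healthcare resources.

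The synopsis names net cost analyses without defining them. Section 10 (Economic Analyses) lists descriptive summaries of resource use only.

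**The concern.** Drug and care are both money spent on the patient. A net cost that subtracts one from the other rewards the arm that uses more hospital care. The purpose of the analysis is to see how far care avoided by the 80 mg dose pays for the extra drug. Under the definition as written, the more hospitalizations and procedures 80 mg prevents, the more expensive it appears.

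The definition also does not say which term holds adverse-event care, although Section 6.5 has that care costed. If it falls in the subtracted term, an arm with more adverse-event care would look cheaper.

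At stake is the cost result for a stated subsidiary objective. No efficacy or safety analysis depends on it.

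**Working it through.** **The plan's own figure.** The protocol gives no net cost figure for this trial, so there is none to reproduce. It does give the 88% from the earlier simvastatin trial, which can test the two readings.

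**Inputs.** T is the cost of lipid-regulating therapy and C is the cost of care incurred for outcomes, both as used in Section 6.5. Subscripts are the arms.

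**Step 1, the definition as written.** Net cost per arm is T - C. The contrast is

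(T80 - C80) - (T10 - C10) = (T80 - T10) + (C10 - C80).

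Taking differences first changes nothing: (T80 - T10) - (C80 - C10) is the same expression. The averted care, C10 - C80, enters with a plus sign either way.

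**Step 2, net of savings, as in the Introduction.**

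(T80 - T10) - (C10 - C80) = (T80 + C80) - (T10 + C10).

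This is the between-arm difference in therapy plus care.

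**Step 3, the gap.** Step 1 minus Step 2 is 2 × (C10 - C80), for any prices.

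**Step 4, test against the 88%.** Set therapy cost in the simvastatin arm at 100 and assume no such cost on placebo. Averted care is then 88. Net of savings: 100 - 88 = 12. By the Section 6.5 wording: 100 + 88 = 188. Only the first matches a statement that 88% of treatment cost was recovered. The gap is 176 = 2 × 88.

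**Step 5, illustration for this trial.** The protocol gives no prices, so the units are assumed: T10 = 1,000, T80 = 3,000, C10 = 900. One row uses a 22% cut in care cost, on the assumption that care cost falls in line with major coronary events. Section 9.1 assumes a five-year "event rate in the atorvastatin 80 mg group of 7.02"% against 9% on 10 mg, and 1 - 7.02/9 = 0.22.

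| Cut in care cost | Care averted | As written | Net of savings | Gap |
|---|---|---|---|---|
| 0% | 0 | 2,000 | 2,000 | 0 |
| 10% | 90 | 2,090 | 1,910 | 180 |
| 22% | 198 | 2,198 | 1,802 | 396 |
| 40% | 360 | 2,360 | 1,640 | 720 |

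As written, the cost of 80 mg rises as it prevents more care. Net of savings, it falls.

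**Step 6, when the sign of the result flips.** With care averted and T80 at least equal to T10, the written form can never show 80 mg as cost-saving. The correct form does so once averted care exceeds the extra therapy cost. For example, if therapy cost were equal in both arms and care fell by 22%, the results would be +198 as written and -198 net of savings.

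**The case against.** The strongest reply is that the parenthesis is shorthand in a list, not a formula. The Introduction shows what is meant, and an analyst who has read it would supply the missing idea of care *averted*. No number in the protocol is wrong, and the costing is done after data collection. Much of this stands: the intent is clear, and the point is properly called a wording error. It does not remove the point. Section 6.5 holds the only definition, its preceding paragraph uses cost of care for cost incurred, and no other section corrects it.

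Two stronger readings are tempting, and the documents support neither.

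- **A reader might infer that the trial cannot resolve the life-year gain behind cost per year of life saved.** The protocol gives no all-cause mortality rate and no assumed effect. With 4,300 patients per arm (assuming equal allocation), two-sided 0.05, and an assumed 10 mg mortality of 4% to 12%, power is 14% to 35% for a 9% reduction, 51% to 95% for 20%, and 87% to over 99% for 30%. The Introduction cites both a non-significant 9% (pravastatin) and a 30% decline (simvastatin). Both come from placebo comparisons and neither transfers directly. The answer depends on inputs the protocol does not give. Section 6.5 also does not confine life-years to the trial period, and a ratio can be reported with its uncertainty without a significant mortality difference.
- **A reader might infer that cost per life-year should give way to cost per cardiovascular event avoided.** That is a preference, not an error in the plan. The list in Section 6.5 is introduced as inclusive, so it does not rule out other ratios.

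**Conclusion.** The definition of net cost in Section 6.5 is wrong as written. It adds averted care to the cost of 80 mg where the Introduction deducts it. The error is exactly twice the averted care cost. That follows by algebra and rests only on reading cost of care as cost incurred, which is how Section 6.5 uses it. The money amounts in the illustration are assumed.

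It would be too strong to say that the conclusion on cost will be reversed. The sign of the result flips only if averted care exceeds the extra therapy cost, and the protocol gives no prices from which to judge that.

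The consequence is limited to the subsidiary economic objective. The primary end point, the secondary clinical end points and the safety analyses are unaffected. It should be corrected because the literal formula gives a wrong answer and the correction costs almost nothing.

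**What to change.** In Section 6.5, redefine net cost as incremental therapy cost minus averted cost of care. Equivalently, it is the difference, 80 mg minus 10 mg, in the sum of therapy cost and cost of care for outcomes and adverse events. State that adverse-event care belongs to the care term, so that it counts as a cost in whichever arm incurs it. Refer to the same definition from Section 10.

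This is a change of wording. The hospitalization and revascularization data are already to be collected, and Section 6.5 already provides for estimating therapy and adverse-event resources. Cost per year of life saved can stay as it is.

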#### **June 13, 2003 – Amendment 4**

#### **6.6 Patient Follow-up/Discontinuation of Study Drug**

Every effort within the bounds of safety and patient choice should be made to have patients complete the study while remaining on study drug. Regardless of their study drug status, all randomized patients should be followed for clinical end points until study completion. Patients are not to be withdrawn from the study drug or followup if they experience a non-fatal clinical end point.

Once randomized, patients should not be discontinued from study drug for noncompliance; they should, however, be counseled on the importance of regularly taking their medication. In general, patients will be encouraged to complete the study and its follow-up for clinical end points, although they may withdraw at any time without prejudice.

Consideration should be given to temporarily withholding or discontinuing the study

drug in any patient with a risk factor or concomitant medication predisposing to the development of renal failure secondary to rhabdomyolysis, including severe acute infection, hypotension, major surgery, trauma, severe metabolic, endocrine, or electrolyte disorders, and uncontrolled seizures.

If a patient becomes pregnant during the trial, study drug should be discontinued and the patient apprised of the potential hazard to the fetus.

Patients prematurely discontinued from study drug during the double-blind phase should have all end-of-study procedures performed (see annual visits beginning at month 24) and may then return to non-protocol lipid therapy. If the final lipid measurements (lipid profile) cannot be performed within 3 days of the cessation of therapy, these measurements should not be performed at all. In this case, the previously determined lipid values will be carried forward for the purpose of analysis.

For patients who withdraw from the double-blind period early, an effort will be made to collect full follow-up information on primary and secondary clinical end points until such time that the study is completed. Methods of follow-up for these patients should include clinic visits when possible according to the timetable (Appendix A) but telephone or mail follow-up should be attempted as well when visits are not possible.

If necessary, an independent search firm will be contracted to locate patients who are lost-to-follow-up at the end of the study to determine if the patient is alive or deceased.

***In order to validly assess the safety and efficacy of the two treatment groups, complete follow-up of all randomized patients is critical. At a minimum, the vital status of every randomized patient must be determined upon study completion. Within local laws and regulations, all sources of data (direct patient follow-up, telephone contact, mail questionnaires, and public sources of information will be utilized in order to ascertain the vital status of each randomized patient.***

Clearly indicate on the appropriate CRF the reason for withdrawal from the study.

## **6.7. Study Completion(f)**

### **June 13, 2003 – Amendment 4**

Unless the study is stopped early as described in Section 9.6.2, patients will complete their participation in the study when the number of ***major coronary events (CHD death, non-fatal myocardial infarction, or resuscitated cardiac arrest)*** is achieved (n = 750) ~~<letter/sentence/paragraph deleted>~~, at which time all patients will have a final annual visit ***(if an annual visit has not been completed in the past 3 months). Subjects not requiring a final clinic visit will be contacted for a final study follow-up/non-clinic visit.*** Clearly indicate on the appropriate CRF the completion date for each patient.

---

(f) See Appendix E, Other Administrative and Regulatory Procedures (Section 3.3, Study Termination)

## 7. STUDY MEDICATION(g)

### 7.1 Formulation

#### June 13, 2003 – Amendment 4

*Pfizer Pharmacy Operations or their designee* will provide medication assembled for each patient based on a randomization code prepared by the Biometrics Department (or their designee).

Each blinded medication container will have a portion of the label that is to be separated from the bottle and attached to the appropriate CRF when the medication is dispensed. Open-label run-in medication will be provided as follows:

#### All Patients

Run-in bottle: atorvastatin 10 mg

Double-blind medication will be provided in a double-dummy format as follows:

|           | Atorvastatin 10 mg Group | Atorvastatin 80 mg Group |
|-----------|---------------------------------|---------------------------------|
| bottle A: | atorvastatin 10 mg              | placebo for atorvastatin 10 mg  |
| bottle B: | placebo for atorvastatin 40 mg  | atorvastatin 40 mg tablets      |

### 7.2. Medication Dispensing

Study medication is to be dispensed by the investigator or the designated hospital pharmacy according to a detailed set of dispensing instructions supplied with the initial shipment of study medication. One bottle of medication must be dispensed at Visit 2 for the atorvastatin 10 mg run-in period and at least two bottles at each visit during the double-blind treatment period. The patient should be instructed to return medication bottles at the next visit and not combine medication from different bottles at any time.

### 7.3. Dosage Regimen

During the open-label run-in atorvastatin period patients will be taking 10 mg once daily and during the double-blind treatment period patients will be taking either 80 mg atorvastatin or 10 mg of atorvastatin once daily. Patients should take 1 tablet daily during the run-in period. During the double-blind treatment period, patients should take 1 tablet from bottle A and 2 tablets from bottle B once daily. Dosing can be at anytime of the day, with or without food, but should be consistent throughout the study.

#### June 13, 2003 – Amendment 4

## 8. DATA COLLECTION

CRFs for all patients will be supplied by ~~letter, sentence, paragraph deleted~~ Pfizer, or their designees. These are to be completed as instructed.(h) Original source documents,

(g) See Appendix E, Other Administrative and Regulatory Procedures (Sections 1.7.2, Medication Code Card and 2.4, Investigational Drug Supply Accountability)

(h) See Appendix E, Other Administrative and Regulatory Procedures (Section 2.2, Guidelines for Recording Data in the Case Report Forms)

CRFs, and other study documents must be maintained at the site as specified.(i) Regular monitoring will be performed by ~~letter, sentence, paragraph deleted~~ Pfizer, or their designees.(j) CRFs will be collected at regular intervals.

## 9. DATA ANALYSIS AND STATISTICAL CONSIDERATIONS

### June 13, 2003 – Amendment 4

#### 9.1. Sample Size Considerations

Assuming a Visit 2 distribution of LDL-C as observed in NHANES III for persons with a history of coronary disease and in the protocol range of 130-250 mg/dl (3.4-6.5 mmol/l), estimated baseline and on-trial levels are as follows:

|                                                                               | Atorvastatin 10 mg                 | Atorvastatin 80 mg |
|-------------------------------------------------------------------------------|-------------------------------------------|---------------------------|
| Mean Visit 2
LDL-C                                                         | 163 mg/dl                                 | 163 mg/dl                 |
| Atorvastatin 10 mg
Run-In                                                  | -35% ± 12%                                | -35% ± 12%                |
| Mean Visits 3 and 4
LDL-C                                                  | 106 mg/dl                                 | 106 mg/dl                 |
| Estimated % > 130 mg/dl
(3.4 mmol/l) @ Visits 3/4
(excluded at Visit 5) | 16%                                       | 16%                       |
| Post-randomization
Reduction in LDL-C                                      | -                                         | -55% from Visit 2         |
| On-Trial LDL-C                                                                | 101 mg/dl                                 | 73 mg/dl                  |
| Difference                                                                    | -28 mg/dl or 0.7 mmol/l (total and LDL-C) |                           |

Using various reported analyses of the relationship between total cholesterol and CHD occurrence, the above differences are estimated to translate to a 20-31% reduction in CHD. A 22% estimate (discounting any effect of triglycerides) is assumed. Finally, a 1.9% annual incidence is assumed in the atorvastatin 10 mg group or approximately 9% over a 5 year treatment duration. This is based on a 28% reduction in the placebo group primary endpoint reported in the CARE trial.

~~Letter, sentence, paragraph deleted~~

(i) See Appendix E, Other Administrative and Regulatory Procedures (Section 2.1.4, Retention of Study Records)

(j) See Appendix E, Other Administrative and Regulatory Procedures (Sections 1.4, Monitoring the Study and 2.3, Review of Case Report Forms)

Assuming a 5 year cumulative **major coronary** event rate in the atorvastatin 80 mg group of 7.02%, a 5 year cumulative **major coronary** event rate in the atorvastatin 10 mg group of 9%, and no dropouts, drop-ins, or noncompliance, a sample size of 6,928 subjects would have 91% power for a one-sided test at alpha of 0.05 and 85% power for a two-sided test at alpha of 0.05. In order to compensate for an estimated 10% dropout/drop-in/noncomplier rate, the study will have a target enrollment of approximately 8,600 subjects  $[6,928/(1-0.1)^2 = 8,553]$  **in order to accumulate the target number of 750 major coronary events in an average follow-up time estimated at 5.5 years** (Lachin, JM, *Controlled Clinical Trials* 2, 93-113 (1981)).

*The sample size estimation shown above was based on assumptions regarding incidence rates for major coronary events (the primary endpoint excluding stroke). It is anticipated that approximately 950 primary endpoints (an additional 200 stroke events) will accrue over the total expected duration of the trial, thereby providing 91% power for a one-sided test at alpha of 0.05 and 85% power for a two-sided test at alpha of 0.05 to detect a 17% reduction in the 5 year cumulative primary endpoint rate for atorvastatin 80 mg relative to atorvastatin 10 mg.*

*<letter, sentence, paragraph deleted>* The power calculations were performed using n-Query Advisor, Version 2.0, by Janet D. Elashoff.

*The steering committee will examine blinded incidence, dropout rate, and other key assumption information when approximately 2 years of completed follow-up data is available and decide whether the proposed target number of events (described in Section 6.1) is appropriate. The sponsor will be approached if a change is proposed.*

#### June 13, 2003 – Amendment 4

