### **9.4. Methods of Analysis**

*All hypothesis testing will be two-sided at a significance level of 0.05 unless otherwise indicated.*

*Subjects who discontinue study medication will continue to be followed to assess the time to occurrence of each endpoint. Subjects who do not experience endpoints during the trial will be considered censored at the time of the data cut-off, death or last contact, whichever is earliest.*

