#### **9.4.1. Primary Efficacy Analysis**

*The null hypothesis that there is no difference in the time to occurrence of a major cardiovascular event between the two treatment groups will be examined using a log rank test. The product limit estimates for the time to occurrence will be calculated and displayed graphically as “survival” curves.*

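### The 85%/91% power stated for the primary endpoint carries no non-adherence allowance unless the 17% is already a net effect, which section 9.1 does not say; with the plan's own 10% allowance it is about 77%/85%

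*Supplement*

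**What the plan says.** All points are in the protocol as amended on June 13, 2003.

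- **Coronary calculation (section 9.1).** The plan assumes a 5-year rate of 7.02% on 80 mg against an "event rate in the atorvastatin 10 mg group of 9%, and no dropouts, drop-ins, or noncompliance, a sample size of 6,928 subjects" that "would have 91% power for a one-sided test at alpha of 0.05 and 85% power for a two-sided test at alpha of 0.05". It then enlarges the trial: "In order to compensate for an estimated 10% dropout/drop-in/noncomplier rate, the study will have a target enrollment of approximately 8,600 subjects", with the arithmetic "6,928/(1-0.1)^2 = 8,553".
- **Primary-endpoint calculation (section 9.1).** Stroke is now part of the primary endpoint. The plan expects about 950 primary events (750 coronary plus 200 strokes) and repeats the earlier pair of figures, "thereby providing 91% power for a one-sided test at alpha of 0.05 and 85% power for a two-sided test at alpha of 0.05", for a 17% reduction in the 5-year cumulative rate. It mentions no allowance here and does not label the 17%.
- **Test (sections 9.4 and 9.4.1).** "All hypothesis testing will be two-sided at a significance level of 0.05 unless otherwise indicated"; the primary null hypothesis "will be examined using a log rank test".
- **Population (section 9.2).** Everyone randomised and dispensed blinded drug is analysed, whether or not they stop it.

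**The concern.** The two power statements in section 9.1 look alike but appear to rest on different footings. In the first, 85%/91% belongs to 6,928 perfectly adherent patients, and the extra 1,600 or so are there to pay for non-adherence. In the second, the same 85%/91% seems to use every enrolled patient at full effect, so the extra patients are spent a second time.

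Dilution is to be expected in this trial. Section 9.2 keeps patients who stop drug in the analysis, section 6.6 lets them return to non-protocol lipid therapy, and sections 5.3 and 6.4.1 permit add-on lipid drugs or open-label atorvastatin in defined circumstances.

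This is the only power statement for the endpoint that is now primary. If the 17% is a full-adherence effect, the type II error is about 23%, not 15%.

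**Working it through.** **Inputs.** From section 9.1: 9% vs 7.02%, N = 6,928, allowance 10%, enrolment 8,600, 950 primary events, 17% reduction. From section 9.4: two-sided alpha 0.05. Assumptions: 1:1 allocation (the ratio is not stated), and 950/8,600 taken as the average cumulative risk.

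**Formula.** Two-proportion test with n per arm, difference d and mean rate p̄:

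power = Φ{ [d√n′ − z√(2p̄(1−p̄))] / √(p1(1−p1) + p2(1−p2)) }

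Here z = 1.960 (two-sided) or 1.645 (one-sided). The continuity correction replaces n by n′, where n = (n′/4)[1 + √(1 + 4/(n′d))]².

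**Step 1. Reproduce the coronary statement.** With n = 3,464, n′ = 3,364, d = 0.0198 and p̄ = 0.0801:

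- numerator: 0.0198 × 58.00 − 1.960 × 0.3839 = 0.396
- denominator: 0.3836
- power: Φ(1.032) = **84.9%** two-sided, and 91.1% one-sided

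This matches. The inflation also matches: 6,928/0.81 = 8,553. The allowance works as intended: 8,600 patients with the difference cut to 0.9 × 1.98 points give 84.8%/91.0%.

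**Step 2. Reproduce the primary-endpoint statement.** With rate ratio 0.83:

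- p1 = 2 × (950/8,600)/1.83 = 12.07%
- p2 = 0.83 × p1 = 10.02%

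All 4,300 per arm are used (n′ = 4,203, d = 0.02052):

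- numerator: 0.02052 × 64.83 − 1.960 × 0.4433 = 0.462
- denominator: 0.4431
- power: Φ(1.042) = **85.1%** two-sided, and 91.3% one-sided

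This also matches, with no allowance.

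**Step 3. Apply the plan's own allowance.** 8,600 × 0.81 = 6,966, or 3,483 per arm (n′ = 3,386):

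- numerator: 0.02052 × 58.19 − 0.8689 = 0.325
- power: Φ(0.734) = **76.9%** two-sided, and 85.3% one-sided

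**Step 4. Vary the method.**

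| Method with the 10% allowance | Two-sided | One-sided |
|---|---|---|
| Effective N 6,966, continuity-corrected | 76.9% | 85.3% |
| Effective N 6,966, uncorrected | 78.0% | 86.2% |
| Risk difference × 0.9, uncorrected | 77.7% | 85.9% |
| Reduction 0.9 × 17% = 15.3%, corrected | 76.2% | 84.8% |
| Reduction 15.3%, uncorrected | 77.3% | 85.6% |
| Log-rank (Schoenfeld), 950 events, log hazard ratio × 0.9 | 78.3% | 86.4% |
| Log-rank, 0.847 entered directly as a hazard ratio | 72.5% | 82.0% |

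The last row is pessimistic because it treats a ratio of cumulative rates as a hazard ratio. Scaling the control rate instead, 9% × 950/750 = 11.4% against 9.46% (uncorrected), gives 83.7%/90.2% for all 8,600 and 75.1%/84.0% for 6,928. The gap is of similar size.

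**Step 5. Which reading do the plan's figures favour?** If the planned 22% coronary reduction holds and stroke is unaffected, the composite reduction is 0.22 × 750/950 = 17.4%. After 10% dilution it would be 15.6%. The event count agrees: the undiluted rates over 5.5 years give 4,300 × [(1 − 0.91^1.1) + (1 − 0.9298^1.1)] ≈ 755, against the target of 750. Both point to a full-adherence 17%. Neither derivation is in the plan.

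**Step 6. What a net 17% would require.** Simple division gives 0.17/0.9 = 18.9% at full adherence. Solving for 85% two-sided power at an effective N of 6,966 gives 18.5% (uncorrected) to 18.7% (corrected).

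**The case against.** The strongest reply is that the printed figure contains no arithmetic error: 950 events and a 17% reduction do give 85%/91%. The full-adherence condition is attached only to the 6,928 calculation, and nothing in section 9.1 attaches it to the 17%. Other origins are possible. A 22% coronary reduction with about a 7% stroke reduction gives (0.22 × 750 + 0.07 × 200)/950 = 18.8%, which is about 17% after 10% dilution. Or the 17% may have been solved for as the difference detectable at the existing 85%, which would explain why the power figures are identical. On either account the 17% is net and the 85% stands. This part of the reply holds, and it is why the point is conditional. It does not excuse leaving the 17% unlabelled: a net 17% needs about 18.5-19% at full adherence, and the plan states that nowhere.

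A reader might also draw three stronger conclusions that the documents do not support.

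- **That the log-rank test gives only 82%/89% before any dilution.** This enters 0.83 as a hazard ratio. The plan's 17% is a reduction in a cumulative rate. The implied hazard ratio is ln(1 − 0.1002)/ln(1 − 0.1207) ≈ 0.82, for which 950 events give about 86% two-sided. The log-rank test therefore supports the undiluted figure.
- **That overlapping strokes would leave fewer first events than 950.** The text already counts about 950 primary endpoints and gives no basis for a lower number.
- **That the steering committee relies on the 85%/91% when it reviews the event target.** Section 9.1 names blinded incidence, dropout and other key assumptions, and does not mention this figure.

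**Conclusion.** The point holds in conditional form. Section 9.1 applies a 10% allowance to the coronary calculation and shows none for the endpoint that is now primary. The stated 85%/91% reproduces only if every one of the 8,600 patients carries the full 17%.

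If the 17% is a full-adherence reduction, as the plan's own figures suggest, power with the allowance is about 76-78% two-sided and 85-86% one-sided. The least favourable method gives about 73% two-sided. No method tried reaches 85%. If the 17% is net, the stated power is right but the full-adherence effect behind it is about 18.5-19%, and that is missing.

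The conclusion rests on 1:1 allocation, on 950 events among 8,600 patients, and on the plan's own convention that a 10% rate dilutes the effect by 0.9. It concerns how the design's power is stated. Type I error, the test and the analysis population are unaffected.

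**What to change.** In section 9.1, say which kind of reduction the 17% is, then use the matching statement:

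- **Full adherence:** with about 950 primary events and the 10% allowance, power is about 77% two-sided (85% one-sided) at alpha 0.05.
- **Net, as randomised:** 85%/91% applies to a net 17% reduction, corresponding to about 18.5-19% at full adherence.

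The cost is a few sentences in section 9.1. On the first reading a published figure becomes less favourable. Enrolment, the 750-event target and the log-rank test need no change.
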